#### Data analysis

All data analysis will be performed using SPSS for Windows V.16.0 (SPSS Inc., Chicago, IL, USA). To avoid bias, the data analyst will be blinded to the data. The per-protocol analysis will be performed in the current study. Participants who successfully complete the study according to the intervention plan would be included in the analysis. The Kolmogorov-Smirnov and Shapiro-Wilk tests will be used to test the normality of continuous data. Normally distributed data will be presented as the mean ± SD, and nonnormally distributed data will be expressed as the median (interquartile range). All quantitative data will be analyzed using methods applicable to between-group (intervention group compared with the control group), within-group (post-intervention data compared with pre-intervention data within the intervention group and the control group, respectively), and between-consequence comparisons. Differences are considered significant when a two-sided *P* value is less than 0.05.

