**Fig. 1 Fig1:**
[figure not shown]
The crossover design of the study

The primary outcome of the study will be the NASA Task Load Index (NASA-TLX) at 07:50 of the next day, which consists of six dimensions rated on a 100-point scale in each dimension (physical demand, mental demand, temporal demand, effort, performance, and frustration) and is widely used to measure the mental workload [22, 23]. Secondary outcomes will be the Chinese Perceived Stress Scale (CPSS), perceived stress scores (visual analogue scale (VAS)), and Multidimensional Fatigue Inventory (MFI-20) scores; the level of satisfaction among participants; heart rate (HR); blood pressure (BP); and incidence of arrhythmia, chest tightness, headache, and palpitations at all the recorded timepoints. The CPSS was used to assess the severity of participants’ psychological stress as earlier reported [24]. Perceived stress score was assessed via the VAS score, which was defined as the length in millimeters from 0 (no stress) to 10 (unbearable stress) [25]. The MFI-20 score was used to quantify the impact of fatigue [26], including five independent subscales of fatigue: general fatigue, mental fatigue, physical fatigue, reduced activity, and reduced motivation.

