### Reporting of compliance and adverse events

To avoid possible bias, participants who had experienced something very pleasant or sad during the washout time will be asked to report their own emotion status before the second enrollment. This would be recorded and judged by two independent psychologists and those who get married or promoted, whose child is born, or whose family member is dead would be excluded from the final analysis. It has been reported that young people are more vulnerable to physical discomfort, such as seizures, severe dizziness, eye twitching, or blackouts triggered by light flashes when wearing a VR headset [29]; therefore, for participants who experience any discomfort during the VR immersion procedure, the trial can be stopped, and the participants will be treated accordingly. All these events are recorded and reported. To ensure the safety of patients, anesthesiologists with the same qualifications will take over the participants’ work during the VR immersion.

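### The only stated analysis set is per-protocol completers, so the NASA-TLX result is conditional on tolerating VR and can favour VR; the symptom comparisons may understate harm

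*Protocol article*

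**What the plan says.** Under Data analysis, the protocol article names the analysis and defines its set: "The per-protocol analysis will be performed in the current study. Participants who successfully complete the study according to the intervention plan would be included". No all-randomised, intention-to-treat or safety set is named anywhere in the article.

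The section Reporting of compliance and adverse events gives two ways of leaving that set after randomisation:

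- **Discomfort on VR.** The text says that "for participants who experience any discomfort during the VR immersion procedure, the trial can be stopped". The same section adds that these events are recorded and reported.
- **Life events in the washout.** The text says that "those who get married or promoted, whose child is born, or whose family member is dead would be excluded from the final analysis". On the assessment of these events it says: "This would be recorded and judged by two independent psychologists". Whether the psychologists are blinded to sequence is not stated.

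The Study design section lists among the secondary outcomes the "incidence of arrhythmia, chest tightness, headache, and palpitations at all the recorded timepoints". Analysis of the secondary outcomes compares these between groups by a chi-square or Fisher test and names no population for the tests.

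**The concern.** The trial asks a superiority question, with a two-sided test at 0.05. In that setting, restricting the analysis to people who completed as planned is generally not the conservative choice, because completion can depend on how the intervention was received.

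Here it does depend on it. Control participants work a routine shift with no headset, so stopping for headset discomfort can happen only on the VR night. The people removed are those in whom VR is least likely to have relieved workload or stress. Because both nights are needed for completer status, removing them also discards any control-night score they gave.

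The same set appears to govern the symptom comparisons. Someone who stopped with a headache on the VR night would then not be counted in the test of headache. At stake are the size of the claimed NASA-TLX benefit, the population it applies to, and the credibility of a finding that symptoms do not differ.

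**Working it through.** **Inputs from Sample size estimation.** NASA-TLX 65.5 before and 55.7 after the intervention in 14 pilot subjects, so the planning effect is 65.5 − 55.7 = 9.8 points. SD 12.1; two-sided alpha 0.05; power 80%; 26 participants before dropout; 10% dropout; 30 in total.

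**Step 1: reproduce the plan's figure.** For a 2 × 2 crossover with N participants, SE = Sw·√(2/N), with N − 2 degrees of freedom and the noncentral t distribution.

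- Taking 12.1 as the within-subject SD (Sw), N = 26 gives SE = 12.1·√(2/26) = 3.36, noncentrality 9.8/3.36 = 2.92 and power 0.800. The stated 26 is reproduced.
- 26/(1 − 0.10) = 28.9, rounded up to 29 and then to 30 for equal sequences.
- The article labels 12.1 as the SD of the difference. The 26 follows only if it is used as Sw, so Sw = 12.1 is kept below to match the plan.

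**Step 2: what the 10% allowance covers.** Completers-only power at an effect of 9.8 is 0.816 with 27, 0.800 with 26 and 0.765 with 24. The allowance protects precision down to 26 completers. It does nothing about a difference between completers and those who stop.

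**Step 3: effect over all randomised participants.** Let q be the share who do not tolerate VR and e their effect. Both are assumptions, since the article gives neither. The effect over everyone is 9.8(1 − q) + e·q.

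| q | e | All-randomised effect | Completers' effect | Power, all 30 analysed |
|---|---|---|---|---|
| 5% | 0 | 9.31 | 9.8 | 0.820 |
| 10% | 0 | 8.82 | 9.8 | 0.778 |
| 20% | 0 | 7.84 | 9.8 | 0.678 |
| 20% | −5 (harm) | 6.84 | 9.8 | 0.561 |

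For the 10% row, SE = 12.1·√(2/30) = 3.12 and noncentrality is 8.82/3.12 = 2.82, which gives 0.778. With e = 0, 80% power with everyone analysed would need 30, 32 and 40 participants for q = 5%, 10% and 20%. These powers hold the SD fixed. If 12.1 really is the SD of the paired difference, power in the 10% row is 0.971; the shift in the effect is the same.

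**Step 4: symptom incidence, worst case.** Assume that the plan's 10% dropout (3 of 30) all stop with a headache on VR and that no completer has one. The completers' table shows 0/27. Among all randomised it is 3/30 = 10%, exact 95% CI 2.1% to 26.5%. The article does not link its dropout allowance to VR, so this is an upper illustration and not a forecast.

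**Step 5: life events.** The washout follows period 1, so an event then cannot have altered the period-1 score, yet the whole participant is dropped. Marriage, promotion, birth and bereavement are not plausible effects of a VR session. The main loss is data.

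**The case against.** Several points on the other side have force.

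- **A reader might infer that harms disappear from the results.** The documents do not support this: the compliance and adverse events section says discomfort events are recorded and reported, and Data collection has the researchers record the symptoms. What stands is narrower. The between-group tests name no population of their own, and applying the per-protocol set to them is an inference, though the natural one given that it is the only set stated.
- **A reader might infer that the randomised comparison is lost altogether.** That is too strong for a crossover. Each completer contributes both nights, intolerance can arise in either sequence, and dropping a person removes both conditions. The main effect is a change of target, to people who tolerate VR.
- **A reader might infer that the life-event rule favours VR.** The events are pre-specified, judged by two psychologists and unlikely to be related to VR.
- **The size is unknown.** Stopping is optional, no rate is given, and the third exclusion criterion may, on one reading, screen out people with previous headset discomfort. At 10% intolerance with no benefit, the shift is about 1 point.
- **A separate analysis set could sit in an analysis plan that is not shown.** For a symptom set, this is fair. For the primary analysis it is not an answer, because the article does not leave the set open: it states per-protocol.

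**Conclusion.** The point holds in this form. A completers-only set is the sole stated analysis of a superiority question, and one route out of it is open only on the VR night. The NASA-TLX estimate therefore applies to those who tolerate VR, and it can be biased in favour of VR. Whether it will be depends on how many stop and how they would have scored, neither of which the article gives.

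Under the assumption that 10% get no benefit, the completers' effect of 9.8 compares with 8.82 over everyone randomised, a gap of 0.98 points. If 20% were affected and were worse by 5 points, the gap would be 2.96. If nobody stops, there is no gap from this source. The symptom tests may understate harm, although the events themselves will be on record. The life-event exclusion is a lesser matter of discarded data after randomisation.

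**What to change.** - **Primary analysis.** Analyse all randomised participants by assigned sequence, using every observed night, in a mixed model with treatment, period and sequence as fixed effects and participant as random.
- **Data collection.** Still obtain the 07:50 assessment when a VR session is stopped, so that those nights have a primary outcome. This leaves the rules on stopping untouched.
- **Sensitivity analyses.** Keep the per-protocol set and the life-event exclusion here, and report how many participants each removes, by sequence and reason.
- **Symptoms.** Report arrhythmia, chest tightness, headache and palpitations by condition for everyone who started that night, and name that population for the between-group tests.

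**Cost.** This is revised analysis wording plus one data-collection instruction. The trial is described as active, so it needs an amendment approved by the IRB. The estimate may be smaller and some power may be lost: about 0.78 with all 30 analysed in the 10% illustration, against 0.816 for 27 completers at the full 9.8. A participant with only one observed night may add little to the within-person contrast, so most of the gain comes from securing the 07:50 score.

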### Data collection

The participants’ general characteristics, including sex, age, body mass index (BMI), heart rate (HR), blood pressure (BP), and electrocardiogram (ECG) data, will be collected. To assess the effect of VR immersion on stress among night-shift anesthesiologists, data will be collected from participants in the intervention group at six timepoints: baseline status (07:50 am, T1), initiation of night shift (17:30, T2), before first VR immersion (23:30, T3), after first VR immersion (23:50, T4) on the day that they work the night shift and before second VR immersion (07:30, T5), and after first VR immersion (07:50, T6) of the next day. At each timepoint, participants will be asked to measure their stress status via completing the scales which included NASA-TLX, CPSS, VAS, and MFI-20. In addition, ECG will be measured using a mobile ECG recorder (CardioLearn; HeartVoice Medical Technology Co., Ltd., Anhui, China) at each timepoint following the manufacturer’s instructions. The mobile device has been widely used in China to simply measure the ECGs and automatically analyze their results based on a novel deep learning-based cloud service as earlier reported [27, 28]. Furthermore, the anesthesiologists will be invited to record their ECG whenever they feel discomfort during the night shift. The incidence of arrhythmia, level of satisfaction, and incidence of chest distress, headache, or heart palpitations will also be recorded by the researchers. The data recording flow chart is presented in Fig. 2 and the SPIRIT figure is shown in Fig. 3.

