### Statistical analysis

#### Sample size estimation

The sample size for this study was estimated using the PASS program 15.0.5. Based on our preliminary data from 14 subjects, the mean ± SD of the NASA-TLX was 65.5 ± 16.8 before the intervention and 55.7 ± 18.2 after the intervention, and the SD of the difference was 12.1. According to tests for the difference between two means in a 2 × 2 crossover design, assuming a two-sided *α* of 0.05 and a statistical power of 80%, 26 participants are needed. To account for a potential dropout rate of 10%, we aim to recruit a sample size of 30 participants in total, and thus, 15 participants are needed for each sequence.

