#### Analysis of the primary outcome

Our primary outcome, the score of the NASA-TLX, will be compared between the two groups, two periods, and two consequences using one-way analysis of variance for the 2 × 2 crossover design.

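### The stated VR-versus-control analyses leave out the pre-VR scores, and the one use spelled out for those scores is before–after tests within each condition, which cannot isolate VR

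*Protocol article*

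**What the plan says.** Under Data collection, all four scales are completed at each of six timepoints. Three precede any VR exposure: T1 (07:50), T2 (17:30, start of the shift) and T3, labelled "before first VR immersion (23:30, T3". The list is written for the intervention group. That pre-VR scores also exist for control nights is implied by the Data analysis section, which plans a before–after comparison there too.

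The endpoint is fixed in the text after Fig. 1: "The primary outcome of the study will be the NASA Task Load Index (NASA-TLX) at 07:50 of the next day", which is T6. Under Analysis of the primary outcome, "Our primary outcome, the score of the NASA-TLX, will be compared between the two groups", and also between periods and sequences, by an analysis of variance for the 2 × 2 crossover. Analysis of the secondary outcomes applies the same method to CPSS, VAS and MFI-20. Neither section names a pre-VR term.

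The use of pre-intervention scores that Data analysis does spell out is "post-intervention data compared with pre-intervention data within the intervention group and the control group, respectively", with a two-sided 0.05 threshold for all comparisons.

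**The concern.** Two things follow from this text.

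First, a before–after test within one condition does not test VR. Scores can move between 17:30 and 08:00 for reasons unrelated to the headset. On VR nights a colleague also takes over the participant's work during each session, so the change includes relief from duty. A significant fall on VR nights alongside a non-significant one on control nights is not a comparison of the two conditions.

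Second, a crossover removes stable differences between persons but not differences between nights. The Setting section gives each participant one night shift per arm, so night-to-night variation stays in the error of the VR-minus-control difference. A score taken the same night before VR can absorb whatever part of that variation it shares with the 07:50 score. At stake are precision in a trial with 26 planned evaluable participants, and a set of P values that a reader could take for evidence about VR.

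**Working it through.** **Inputs from Sample size estimation.** "the mean ± SD of the NASA-TLX was 65.5 ± 16.8 before the intervention and 55.7 ± 18.2 after the intervention", so δ = 65.5 − 55.7 = 9.8; "the SD of the difference was 12.1"; "assuming a two-sided *α* of 0.05 and a statistical power of 80%, 26 participants are needed".

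**1. The plan's own figure.** Two-sided t-test for a 2 × 2 crossover, df = N − 2, non-centrality = δ / (SD_d/√N), where SD_d is the SD of the between-night (VR minus control) difference.
- 12.1 read as the within-subject SD: SD_d = 12.1 × √2 = 17.11. At N = 26 the non-centrality is 9.8 / (17.11/5.099) = 2.92 and power is 0.800; at N = 24 it is 0.765. This reproduces 26.
- 12.1 read as SD_d itself: non-centrality 9.8 / (12.1/5.099) = 4.13, power 0.977 at N = 26, and 16 participants would suffice. This does not give 26.

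**2. What the within-condition tests detect.** Paired t-test, n = 26, df = 25, before–after SD 12.1, no VR effect, and an assumed drift x from time of night alone. Non-centrality = x / (12.1/√26) = x / 2.373.

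| Assumed drift x | Probability of P < 0.05 |
|---|---|
| 0 | 0.05 |
| 3 | 0.23 |
| 5 | 0.53 |
| 9.8 | 0.98 |

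Four scales in two conditions make at least 8 such tests. Even with no drift, the chance of at least one false positive is 1 − 0.95⁸ = 0.34 if they are independent.

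**3. Gain from adjusting the between-condition comparison.** Let ρ be the correlation between the between-night difference in T3 and the between-night difference in T6. The documents do not give it, so it is assumed over a range. Adjusted SD = 17.11 × √(1 − ρ²), df = N − 3 = 23.

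| ρ | Adjusted SD | Variance reduction | Power at N = 26 |
|---|---|---|---|
| 0 | 17.11 | 0% | 0.799 |
| 0.1 | 17.03 | 1% | 0.802 |
| 0.2 | 16.77 | 4% | 0.814 |
| 0.3 | 16.32 | 9% | 0.834 |
| 0.5 | 14.82 | 25% | 0.898 |
| 0.6 | 13.69 | 36% | 0.937 |

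**4. A rough placing of ρ.** The pilot figures imply a before–after correlation of (16.8² + 18.2² − 12.1²) / (2 × 16.8 × 18.2) = 467.07 / 611.52 = 0.764. Assume that it holds for T3 and T6 of one night, and that any two scores from different nights share one correlation r_b = 1 − 17.11² / (2·SD²). Then ρ = (0.764 − r_b) / (1 − r_b).
- SD 16.8: r_b = 0.481, ρ = 0.545, power 0.915.
- SD 18.2: r_b = 0.558, ρ = 0.466, power 0.885.

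This is only an illustration. The spacing of the pilot's two measurements is not stated, whereas T3 and T6 are more than eight hours apart.

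**5. If SD_d is 12.1.** Unadjusted power is already 0.977, and adjustment at ρ = 0.3 gives 0.985.

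**6. Covariate rather than change score.** With equal variances, the variance ratio against no adjustment is 2(1 − ρ) for a plain change score and 1 − ρ² for the covariate: 1.40 against 0.91 at ρ = 0.3, 1.00 against 0.75 at 0.5, 0.80 against 0.64 at 0.6. Below ρ = 0.5 the change score does worse than no adjustment.

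**The case against.** The strongest reply is that leaving out a covariate is not an error. The randomised crossover comparison at 07:50 is unbiased without it, the design already removes stable differences between persons, and covariates are often settled in an analysis plan, which is not shown here. The statement about unbiasedness stands. But the article does name its model and does commit to the within-condition tests, so the point concerns stated text and not missing detail.

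It can also be said that Data analysis applies between-group methods to all quantitative data, so a between-group use of pre-VR scores is not excluded. That is fair: within-condition testing is the only use spelled out, not provably the only use intended.

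A reader might infer more than the documents support:
- That the trial will claim efficacy from a within-group fall. The Abstract and the primary analysis both rest on the between-group difference.
- That regression to the mean drives the within-group change. The eligibility criteria do not select on a high stress or workload score.
- That the difficulty of the night is the main source of noise. No data show this, and the criteria narrow case mix to ASA I–II and operations of 2 to 4 h.
- That a definite power gain is being lost. ρ is unknown, and the SD of 17.1 follows only from reading 12.1 as a within-subject SD.

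Finally, relief by a colleague is part of the VR condition in the between-condition contrast as well. Adjustment does not remove it.

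**Conclusion.** The point holds in a limited form. The within-condition significance tests cannot distinguish VR from change over the night, and this does not depend on any assumed correlation. Their 0.53 chance of significance under a 5-point drift rests on n = 26, an SD of 12.1 and an assumed drift.

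Leaving the pre-VR score out of the crossover analysis costs precision, not validity. The loss runs from nothing (ρ = 0) to about 14 percentage points of power (ρ = 0.6) if SD_d is 17.1, and is negligible if SD_d is 12.1. In the worst case adjusting lowers power from 0.800 to 0.799, so it is a cheap improvement that should be specified in advance. The documents do not support reading this as a flaw that invalidates the primary comparison.

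**What to change.** - In the 2 × 2 crossover analysis of the T6 NASA-TLX, and of CPSS, VAS and MFI-20, add the same night's T3 score as a covariate through its within-participant between-night difference. Equivalently, regress each participant's period 1 minus period 2 difference in T6 on sequence and on the same difference in T3; half the sequence coefficient is the VR effect.
- Repeat with T2 in place of T3 as a sensitivity analysis, because participants are not blinded and their 23:30 score may reflect anticipation of VR.
- State that T2 and T3 are collected on control nights as well.
- Do not use T5 as a baseline, or T5 to T6 as an effect measure for the whole intervention. T5 follows the first VR session, so any lasting benefit of that session would be subtracted.
- Report changes within each condition descriptively, without significance tests.

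The cost is analysis wording and one degree of freedom, with no new data if control-night scores are collected as implied. The remaining downside is possible anticipation in T3. The rest that comes with the colleague's takeover on VR nights stays in the contrast and should be acknowledged when the result is interpreted.

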#### Analysis of the primary outcome

Our primary outcome, the score of the NASA-TLX, will be compared between the two groups, two periods, and two consequences using one-way analysis of variance for the 2 × 2 crossover design.

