## Methods/design

### Study design

The virtual reality immersion in the night-shift anesthesiologist trial is a randomized controlled, single-center clinical trial using a crossover design with a washout of 1 week. Anesthesiologists will be randomized in a 1:1 allocation to a sequence of either immersion relaxation using VR in the first period, followed by no immersion VR in the second treatment period, or no immersion VR in the first period, followed by immersion relaxation using VR in the second period. Anesthesiologists undergoing VR intervention will undergo immersion relaxation via VR twice during the night shift: the first session will occur at 23:30, and the second session will occur at 07:30 the next day. The anesthesiologists will be able to choose VR content and enjoy themselves for 20 min. Anesthesiologists in the control group will not watch VR videos during the night shift. The design of the study is presented in Fig. 1.

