#### Analysis of the secondary outcomes

The effect of VR immersion on the CPSS, VAS, and MFI-20 scores will be compared using one-way analysis of variance for the 2 × 2 crossover design. Spearman’s rank correlation test will be used to analyze the association between work hours and scores on the scales. The age, BMI, HR, MBP, and the level of satisfaction between groups will be analyzed by the Student *t* test or the Wilcoxon rank-sum test. The gender, incidence of arrhythmia, chest distress, headache, and heart palpitations between groups will be analyzed by the Pearson *χ*^2^ test or Fisher’s exact test.

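### The primary analysis is named as a one-way ANOVA, which has no participant term and cannot fit treatment, period and sequence together; followed literally, it gives about 51% power instead of the stated 80%

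*Protocol article*

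**What the plan says.** The Study design section describes a trial "using a crossover design with a washout of 1 week", in which each anesthesiologist is randomized to VR then no VR, or the reverse. The Setting section adds that each person works one night shift per arm. The endpoint gives one value per person per night: "The primary outcome of the study will be the NASA Task Load Index (NASA-TLX) at 07:50 of the next day".

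Analysis of the primary outcome sets the treatment groups against each other, together with "two periods, and two consequences using one-way analysis of variance", and ties that ANOVA to the crossover design. 'Consequences' evidently means sequences. Analysis of the secondary outcomes says that the CPSS, VAS and MFI-20 "scores will be compared using one-way analysis of variance", again with the crossover phrase attached. For HR, mean blood pressure, satisfaction and symptom incidence, that section names independent-samples tests (Student t or Wilcoxon rank-sum, Pearson χ² or Fisher).

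Sample size estimation uses a test for two means in a 2 × 2 crossover, two-sided α 0.05 and 80% power, and arrives at 26 participants, raised to 30 for dropout. Its pilot inputs come from 14 subjects. The means and their spread are given as follows: "the mean ± SD of the NASA-TLX was 65.5 ± 16.8 before the intervention and 55.7 ± 18.2 after the intervention". The remaining input, on which the calculation turns, is the variability of the change: "the SD of the difference was 12.1".

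**The concern.** Every participant supplies two scores, one from a VR night and one from a control night, and the two are correlated. A one-way ANOVA handles one factor and assumes independent observations. Applied to this trial it would treat a person's two nights as two different people, leave between-person variation in the error term, and make no adjustment for period. The sample size, by contrast, comes from a crossover test whose error term is within-person variation. The named analysis and the planned power therefore do not match.

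Two errors in opposite directions follow from the literal method. The treatment comparison gets a standard error that is too large, so the interval is too wide and a real effect is easier to miss. The sequence comparison gets a standard error that is too small, because two correlated values per person are counted as independent, so it can signal carry-over that is not there.

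**Working it through.** **Inputs (Sample size estimation).** Effect δ = 65.5 − 55.7 = 9.8; marginal SDs 16.8 and 18.2; a figure of 12.1 labelled as the SD of the difference; two-sided α 0.05; N = 26 before dropout.

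**Reproducing the plan's N.** Crossover t-test, noncentral t, df = N − 2, SE = SD of paired difference / √N.
- 12.1 entered as the within-subject SD: SD of paired difference = 12.1 × √2 = 17.1. N = 26 gives power 80.0%, and N = 24 gives 76.5%. This reproduces the stated 26.
- 12.1 used as the SD of the paired difference, as labelled: N = 16 is enough (85.3%; N = 14 gives 79.4%), and 26 would give 97.7%.

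The first reading matches the planned N, so it is the main case. The second is the sensitivity case.

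**Correlation between a person's two scores.** r = (16.8² + 18.2² − SD_diff²) / (2 × 16.8 × 18.2), where 16.8² + 18.2² = 282.24 + 331.24 = 613.48 and the denominator is 611.52.
- SD_diff = 17.1: (613.48 − 292.82) / 611.52 = 0.52.
- SD_diff = 12.1: (613.48 − 146.41) / 611.52 = 0.76.

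**Crossover analysis at N = 26 (df 24, t = 2.064).**
- r = 0.52: SE = 17.1 / √26 = 3.36; half-width 2.064 × 3.36 = 6.9.
- r = 0.76: SE = 12.1 / √26 = 2.37; half-width 2.064 × 2.37 = 4.9.

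**Literal one-way ANOVA at N = 26 (52 values taken as independent, df 50, t = 2.009).** SE = √(613.48 / 26) = 4.86; half-width 2.009 × 4.86 = 9.8; power by the independence formula 50.8%.

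**Simulation** (200,000 trials per setting, bivariate normal, 13 per sequence, no period effect):

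| | r = 0.52 | r = 0.76 |
|---|---|---|
| Power, one-way treatment test | 51% | 52% |
| Power, crossover analysis | 80% | 98% |
| 95% CI half-width, one-way against crossover | 9.8 against 6.9 | 9.8 against 4.9 |
| Ratio of half-widths | 1.4 | 2.0 |
| True size of one-way treatment test (nominal 5%) | 0.6% | 0.03% |
| False rejection, one-way sequence test (no treatment effect) | about 12% | about 15% |

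The sequence figures agree with a large-sample check. Ignoring the correlation understates the variance of the sequence difference by a factor 1 + r, so the rejection rate is P(|Z| > 1.96 / √(1 + r)): about 11% at r = 0.52 and 14% at r = 0.76.

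**If all 30 complete.** Formula power is 57% for the one-way test, against 85.7% (r = 0.52) or 99.0% (r = 0.76) for the crossover analysis. The 10% dropout allowance does not close the gap.

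**The case against.** The strongest reply is that this is a misnomer. The sentence ties the ANOVA to the 2 × 2 crossover design and lists groups, periods and sequences, which are the terms of a crossover ANOVA. The sample size uses a crossover test, and the full analysis plan is not shown. This stands to the extent that the article does not prove that unpaired tests are intended, and it does not say that three separate one-factor tests will be run. It does not rescue the wording. The method named is still one-way, no participant term or paired method appears anywhere, and the independent-samples tests planned for other outcomes recorded under both conditions point the same way. This is a stated method that conflicts with the design, not detail left to another document.

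A reader might draw three stronger conclusions that the documents do not support.
- *The interval is twice too wide and power falls from 98%.* That takes 12.1 as labelled, under which the plan's 26 does not reproduce. It also assumes that a before/after pilot correlation applies to two separate nights. On the reading that yields 26, the ratio is 1.4 and the contrast is 51% against 80%.
- *All the benefit of crossing over is lost.* Even the literal test keeps two nights per person. A parallel trial of 26 people, 13 per arm, would have about 28% power on the same SDs. Only the within-person part of the gain goes.
- *False claims of VR benefit become more likely.* The treatment test is conservative. With equal sequences a period effect largely cancels from the treatment difference, so leaving period out costs mainly precision unless exclusions are uneven.

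**Conclusion.** The concern holds as a defect in the named method. As written, the primary analysis does not fit the design and would not deliver the stated power: about 51% instead of 80% with 26 completers and a 9.8-point effect, a confidence interval 1.4 times too wide, and a true type I error near 0.6%. Power of the literal test stays close to 51% under either reading of the 12.1; what changes is how much the proper analysis would have gained.

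These figures rest on the literal reading of the method, normal scores, no period effect, and the pilot SDs applying to the trial nights. Whether the authors intend a proper crossover ANOVA cannot be settled from the article. The text needs correcting either way, because it governs the only primary outcome and three secondary scales.

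**What to change.** Replace the primary-analysis sentence with wording such as:

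> NASA-TLX at 07:50 (T6) will be analysed by a crossover ANOVA or linear mixed model with fixed effects for treatment, period and sequence, and participant (within sequence) as a random effect. The VR-minus-control difference will be reported with its 95% confidence interval.

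For complete 2 × 2 data, a t-test on within-person period differences, compared between sequences, gives the same treatment test, so either form is acceptable. Any sequence comparison should use the between-participant error. Use the same model for CPSS, VAS and MFI-20.

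The cost is wording only: no extra participants or data. If a crossover ANOVA was always meant, the change simply records it.
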